### Data Management and Data Analysis

Quantitative data collection will be done using electronic forms developed in the Open Data Kit, and all data will be securely stored in the cloud with access only to the research team. The recordings of the in-depth interviews and FGDs will be transcribed to the local languages, translated to English, and analyzed by 2 independent researchers using open, inductive coding and content analysis. Similar phrases with recurring themes will be coded in NVivo (QSR International). Quantitative data will be collected in the KoboCollect (Kobo Inc) mobile phone app. Data analysis will be done in the software package SPSS Statistics (SPSS Inc). Simple descriptive methods will be used to generate a demographic profile of the study sample. Differences between participants in the groups (audio, written materials, and control groups) will be evaluated using the Mann-Whitney *U* test or 1-tailed *t* test for continuous variables and the chi-square statistic for categorical variables. The mean (SD) or median (IQR), depending on the distribution of the data, of the total scores of the scales used will be calculated per intervention area. Stepwise multivariate regression with backward elimination will be done to examine what factors will have an independent effect on the outcomes. We will calculate the percentage change and corresponding 95% CI before and after the interventions are implemented and the statistical significance of this difference using a z test for differences between proportions. Effect sizes will also be calculated. If necessary, we will correct for differences in demographic information between study arms using quantile regression. We will compare the differences in follow-up assessment between the audio-delivered and written interventions. The knowledge gaps, beliefs, misconceptions, fears, etc identified in the baseline study will be summarized into a narrative review and will be used by the persons affected by leprosy group as input for the development of the content of the interventions. The most appropriate modes of delivery will be determined based on the communication needs assessment that will be conducted as part of the baseline study. The interventions will be developed using participatory methods.

Confidentiality and anonymity of data will be ensured in data collection, storage, analysis, and publication. Research assistants who will collect the data will be trained in data management, the maintenance of confidentiality, and ensuring privacy during data collection. Data will only be analyzed and shared with the Dutch and German researchers (outside of Nigeria) when they have been fully anonymized. The lead applicant will take full responsibility for ensuring the appropriate storage and security of data. Data will be kept for 5 years and destroyed after this time frame when no longer required.

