### Study Location and Setting

The study will be carried out in 6 local government areas (LGAs), 3 each in Cross River State (Boki, Calabar-South, and Obubra) and Taraba State (Jalingo, Yorro, and Zing). The 3 LGAs per area will be selected based on similarity in terms of literacy rate and prevalence of leprosy. Cross River is located in southern Nigeria, while Taraba is in the north. The total population of the study area is 940,540, estimated from the 2006 census, with 542,494 in Cross River and 398,046 in Taraba states. Both states have been selected because of the high prevalence of leprosy and G2D.

Cross River State notified a total of 106 new cases (17% with G2D) in 2019. The most common language spoken in Cross River State is Nigerian Pidgin. Over 90% of the people living in the selected LGAs in southern Nigeria speak Nigerian Pidgin. Other languages spoken in Cross River State include Efik, Ekoi, and Yala. The illiteracy rate (those with no schooling or primary or secondary education who cannot read at all) is 12.2% and 26.4% for male and female individuals, respectively. Occupations include farming, trading, and civil service employment. About 58% of women own mobile phones, compared with 71% among men [40]. Cross River State’s poverty index is 0.146, and the poverty headcount rate is 36.3%. The case notification rate for leprosy is 2.76 per 100,000 people based on 2020 data.

Taraba is among the 15 high-burden states for leprosy in Nigeria; an average of 100 new cases were detected between 2013 and 2017, with an average of 6% and 5% of children and G2D cases, respectively. This figure is likely to be underreported, considering the significant presence of isolated populations such as nomadic pastoralists and internally displaced people in the state.

The most common language spoken in the selected LGAs in Taraba State is Hausa; 80% to 90% of the people living in the selected LGAs in Northern Nigeria speak Hausa. Other languages spoken in Taraba State include Mummuye and Fulfulde. The illiteracy rate is 30.1% and 64.9% in Taraba State for male and female individuals, respectively. Occupations in Taraba include farming, mainly crop production and cattle rearing, petty trading, and civil service employment. The majority of men (71%) own a mobile phone, while only 44.6% of women do. Taraba State’s poverty index is 0.448, and the poverty headcount rate is 87.7%. The case notification rate for leprosy is 2.30 per 100,000 people.

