### Study Duration and Sample Size Calculation

This study’s duration will be 2 years. The sample size for the various components of the study is as follows. (1) A total of 200 community members (100 for each language per study area) will be included in the cross-cultural validation of the Explanatory Model Interview Catalogue Community Stigma Scale (EMIC-CSS) and Social Distance Scale (SDS), while 100 persons affected by leprosy (50 for each language per study area) will be included in the cross-cultural validation of the Internalized Stigma of Mental Illness (ISMI) scale and Rosenberg Self-Esteem Scale (RSES; see below). (2) A total of 770 community members will be included in the baseline and follow-up questionnaire interviews. This means a random sample of at least 385 persons in Taraba State (northern Nigeria) and at least 385 persons in Cross River State (southern Nigeria), which will consist of 114 in the audio intervention group, 114 in the written material intervention group, and 157 in the control group in each region.

This RCT will have three arms: (1) an audio-delivered intervention group, (2) a written material intervention group, and (3) a control group. The sample size calculation is based on 2 calculations. The intervention group calculation is based on an estimate of the difference in knowledge improvement between the audio-delivered intervention and the written material intervention groups. We used data from a perception study in India. In this study, postintervention scores improved by 12.5% after a poster intervention and community meetings. We estimate that the effect of posters alone would be an increase of 10%. We want to be able to detect an improvement of at least 15% between the audio-delivered and the written material intervention groups. The sample size of the intervention group is therefore based on a proportion 1 of 10 (estimated percentage of improvement in knowledge of leprosy in the written intervention group) and a proportion 2 of 25 (ie, an improvement of 15% or more). With a power of 80%, a significance level of .05, and a 15% loss to follow-up, 114 participants are needed in each intervention group.

We expect an increase of 2% in the knowledge score in the control group. The control group calculation is therefore as follows: proportion 1:10, proportion 2:2, power 80%, significance .05, and 15% loss to follow-up, resulting in 157 participants.

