### Participant Recruitment and Follow-Up

Persons affected by leprosy and community members will be selected based on purposive sampling. They will develop the content of the interventions. This is therefore, ideally, a diverse group of people who represent multiple perspectives. We will select participants based on purposive sampling to ensure adequate representation of age, gender, and villages.

The intervention will be implemented in North and South Nigeria, 2 areas that are very different. Therefore, we will cluster-randomize the interventions to ensure comparable groups are included in both areas. There are three different “groups” in each site (North and South): (1) the audio-delivered intervention, (2) the written materials intervention, and (3) no intervention (control group).

We will select 3 LGAs in North and South Nigeria (6 in total); each LGA will have either the audio-delivered or the written intervention or be a control group. The three LGAs per area will be selected based on their similarity in terms of literacy rate and endemicity of leprosy.

The interventions will be randomly allocated to clusters (LGAs) based on a random numbers list. This is a 2-stage random sampling. We will select a random sample of LGAs and a random sample of participants within each LGA. The participants in each LGA will be selected using the “spin the bottle” approach: a bottle will be spun in front of the most central place in the village (rural area) or neighborhood (urban area); the direction the bottle points at is the direction we start walking and counting. The first house to be included is selected by casting a die. Participant selection will be done by proportional sampling among the clusters. We will include the same participants at baseline and follow-up (a paired sample). This study protocol is reported in accordance with the SPIRIT statement (see checklist in Multimedia Appendix 1). The timeline schedule for participants during the study period is represented in Table 1, and a schematic description of the study flow chart is depicted in Figure 1.

**Table 1 table1:** Study schedule for enrollment, intervention, and assessment.

Schedule				Study period and time point										
				Enrollment		Allocation		Postallocation						Close out
				t_–1_		t_0_ (month 0)		t_1_ (baseline)		t_2_ (intervention)		t_3_ (6 months follow-up)		t_4_

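### Arms are allocated by LGA (two per arm), but the named between-arm tests treat participants as independent, so LGA differences can be declared intervention effects far more often than 5% of the time

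*Protocol article*

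**What the plan says.** On design, Study Location and Setting states: "The study will be carried out in 6 local government areas (LGAs), 3 each in Cross River State", with the other three in Taraba. Participant Recruitment and Follow-Up states: "The interventions will be randomly allocated to clusters (LGAs) based on a random numbers list", and "each LGA will have either the audio-delivered or the written intervention or be a control group". That makes six randomised units, two per arm overall and exactly one per arm within each state.

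On analysis, Data Management and Data Analysis states: "Differences between participants in the groups (audio, written materials, and control groups) will be evaluated using the Mann-Whitney" U test or a one-tailed t test for continuous variables and chi-square for categorical ones. It adds a backward-elimination regression, a z test on before-and-after proportions, and quantile regression if demographics differ between arms. No LGA effect, cluster-robust variance or LGA-level summary analysis is stated.

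On size, Study Duration and Sample Size Calculation gives "114 in the audio intervention group, 114 in the written material intervention group, and 157 in the control group in each region", and justifies the intervention arms thus: "With a power of 80%, a significance level of .05, and a 15% loss to follow-up, 114 participants are needed in each intervention group". No ICC or design effect appears. The Limitations section mentions variable cluster size and contamination, but not correlation within LGAs or the small number of LGAs.

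**The concern.** People in one LGA share a health service, language mix, local beliefs and local events over the six months of follow-up, so their outcomes are correlated. A participant-level test ignores this. Its standard error is too small, and a real difference between places can be read as a difference between interventions. Within one state the problem is total: arm and LGA are the same variable, and no analysis can separate them.

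At stake are the answer to the primary objective (impact of audio and written education on perception) and the audio-versus-written comparison in secondary objective 2. The Conclusion offers the results to policy makers as reliable evidence.

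**Working it through.** **1. Reproduce the plan's own sample sizes.** Inputs from Study Duration and Sample Size Calculation: 10% vs 25% (written vs audio), 10% vs 2% (written vs control), power 80%, significance .05 (taken as two-sided), loss 15%. Formula for two independent proportions:

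n = (1.960 + 0.842)² × [p1(1−p1) + p2(1−p2)] / (p1−p2)², then divide by 0.85.

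- 10% vs 25%: 7.849 × (0.09 + 0.1875) / 0.15² = 96.8; 96.8 / 0.85 = 113.9. Stated: 114.
- 10% vs 2%: 7.849 × (0.09 + 0.0196) / 0.08² = 134.4; 134.4 / 0.85 = 158.1. Stated: 157, a close match.

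Both are sizes for individual randomisation, that is, a design effect of 1.

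**2. Type I error of a participant-level test.** Retained per intervention LGA: m = 114 × 0.85 ≈ 97. The ICC is an assumption, shown as a range.

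- Design effect: DE = 1 + (m − 1) × ICC = 1 + 96 × ICC.
- True two-sided error of a nominal 5% test: 2 × [1 − Φ(1.96/√DE)].
- True one-sided error of a nominal 5% test: 1 − Φ(1.645/√DE).

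| Assumed ICC | DE | Two-sided 5% test | One-sided 5% test |
|---|---|---|---|
| 0.005 | 1.48 | 10.7% | 8.8% |
| 0.01 | 1.96 | 16.2% | 12.0% |
| 0.02 | 2.92 | 25.1% | 16.8% |
| 0.05 | 5.80 | 41.6% | 24.7% |

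A beta-binomial simulation (100,000 runs, 10% outcome, 97 per LGA, two LGAs per arm) gave two-sided errors of 10.7%, 16.3%, 25.1% and 41.7%, in line with the formula.

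**3. Degrees of freedom of a valid analysis.** Six LGA means, less one intercept, two arm terms and one state term, leave 6 − 1 − 2 − 1 = 2 residual degrees of freedom. The two-sided 5% critical value is 4.30.

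**4. Power of that analysis for 10% vs 25%.** With two LGAs of 97 per arm, SE = √[0.2775/(2 × 97) × DE]. A noncentral t on 2 degrees of freedom with noncentrality 0.15/SE gives power of about 56% at ICC 0, 36% at 0.01, 27% at 0.02 and 17% at 0.05. The stated 80% is not reached even with no clustering at all.

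**5. Why a mixed model is not a safe substitute.** With 2 residual degrees of freedom and roughly equal LGA sizes, the ratio of between-LGA to within-LGA mean square is approximately DE × χ²(2)/2. The LGA variance is estimated as zero when this ratio falls below 1, with probability 1 − exp(−1/DE): 0.40, 0.29 and 0.16 at ICC 0.01, 0.02 and 0.05. In those trials the model falls back to the participant-level standard error unless the degrees of freedom are fixed by hand.

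**The case against.** **The quoted sentence may describe a baseline check.** It follows the sentence on the demographic profile, and the later sentence on comparing audio with written at follow-up names no test. This reading is possible. It does not remove the problem, because no cluster-aware method is stated for any comparison and the sample size also ignores clustering. An unseen analysis plan may add detail, but the article itself fixes participant-level tests.

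**The regressions might include LGA.** The candidate factors are not listed, so one can say only that no LGA term is stated. That stands as a limit on the wording.

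**The ICC may be small.** LGAs are chosen to be alike in literacy and leprosy endemicity, and the same people are measured twice. Both may lower the ICC for change. Neither removes change specific to an LGA, and an ICC of 0.005 already doubles the error.

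Some stronger readings are tempting but not supported:

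- That false positives will occur, or are to be expected. The error rates depend on an assumed ICC and stay below one half over this range.
- That every objective is affected. Secondary objective 1 is descriptive, and arm-by-gender contrasts compare men and women within the same LGA, where differences in LGA level cancel.
- That the z test belongs here. It is a before-and-after test, so stable differences in LGA level cancel; its neglect of pairing is a separate matter.
- That false positives accumulate over separate tests in each state. The analysis section states no such tests, although the sample is sized by state.
- That a randomisation test could never give a two-sided p below 0.5. This holds only with the control LGAs held fixed (2 of 4 arrangements). Over all 36 within-state allocations the minimum is 2/36 = 0.056.

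**Conclusion.** The point holds: the between-arm methods named in the article contradict its allocation by LGA. Under no intervention effect, a nominal two-sided 5% test rejects about 16%, 25% or 42% of the time at an ICC of 0.01, 0.02 or 0.05, and a one-sided 5% test about 12%, 17% or 25%. These figures assume 97 retained per intervention LGA and an ICC that the document does not give; the direction of the error depends on neither, as long as the ICC is above zero. The arm comparisons in the primary objective and in secondary objective 2 are affected. An LGA-level analysis makes the inference valid but cannot restore power, and single-state arm contrasts stay fully confounded with place under any analysis.

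**What to change.** In Data Management and Data Analysis:

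- Make the LGA the unit of inference for every arm comparison. Regress the six LGA-level mean changes (or baseline-adjusted means) on arm and state, with t on 2 residual degrees of freedom (critical value 4.30).
- Report pooled estimates with the confidence intervals from this model, and no arm p-values within a single state.
- State that participant-level p-values are not evidence of effect, and that the trial gives estimates rather than a confirmatory test.
- Do not offer a mixed model as an interchangeable alternative, because with six LGAs its variance estimate and degrees of freedom are unreliable.

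In Study Duration and Sample Size Calculation, state that the 80% power assumes no clustering and is not delivered by two LGAs per arm.

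The cost is much wider confidence intervals and the loss of the confirmatory claim. Enrolment and allocation need not change. The Results section says that neither implementation nor data analysis had begun at submission, so as of that date the change could be made before any outcome comparison.

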### Primary and Secondary Objectives

Our primary objective is to assess the impact of audio-delivered and written health education on the perception of leprosy in Nigeria. Additionally this study has the following secondary objectives: (1) to investigate the perception (local beliefs, knowledge, and attitudes) of community members toward leprosy and persons affected by leprosy; (2) to investigate whether there is a difference in impact on perception between participants who have received audio-delivered health education and those who have received written health education, with specific reference to gender differences and differences between rural and urban areas; and (3) to assess the impact of the participatory development of the audio and written interventions on empowerment and internalized stigma of persons affected by leprosy who developed the interventions.

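### A one-tailed t test is named for continuous differences between arms, with no direction, level or reason, although the objective is non-directional and the sample size fits two-sided testing

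*Protocol article*

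**What the plan says.** Under Data Management and Data Analysis, the protocol says that the three groups will be compared by Mann-Whitney "or 1-tailed *t* test for continuous variables and the chi-square statistic for categorical variables". The sentence does not say which direction the one-tailed test takes, at what level it is run, or why one tail was chosen. The same section plans 95% confidence intervals for percentage change, effect sizes, and "the statistical significance of this difference using a z test for differences between proportions". Neither that z test nor the Mann-Whitney or chi-square test is labelled one-tailed.

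Under Primary and Secondary Objectives, the second of the secondary objectives is "to investigate whether there is a difference in impact on perception between participants who have received audio-delivered health education", compared with recipients of the written form. It names no expected direction.

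Under Study Duration and Sample Size Calculation, the written group enters the first calculation as "proportion 1 of 10 (estimated percentage of improvement in knowledge of leprosy in the written intervention group"). For the audio group, the figure entered is "a proportion 2 of 25 (ie, an improvement of 15% or more"). The result is given as: "With a power of 80%, a significance level of .05, and a 15% loss to follow-up, 114 participants are needed in each intervention group". The control group is sized on "proportion 1:10, proportion 2:2, power 80%, significance .05, and 15% loss to follow-up, resulting in 157 participants". Neither calculation says whether .05 is one-sided or two-sided.

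**The concern.** A one-tailed test answers a directional question, so the direction has to be fixed in advance and defended. Here there are three pairwise contrasts among the arms and more than one community measure (knowledge, community stigma, social distance). No tail is assigned to any of them, so nothing in the text prevents the tail from being chosen once the data are known.

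The label also separates one test from the rest of the plan. The section reports means or medians according to the distribution of the data, so the choice between the t test and Mann-Whitney presumably follows the same rule. If it does, the evidence needed to claim a difference on a scale could depend on how normal its scores look.

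Two things are at stake for continuous scores: a lower bar for a claim in the favoured direction, and no formal claim from the t test if the result goes the other way. A finding that written material did better than audio, or that attitudes worsened after education, would matter to the policy makers and programme managers whom the protocol's conclusion addresses.

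**Working it through.** **Inputs.** From the sample size section: 10% against 25% (written against audio), 10% against 2% (written against control), level .05, power 80%, loss 15%. Normal quantiles: 1.960 (two-sided .05), 1.645 (one-sided .05), 0.842 (80% power).

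**1. Reproduce the plan's figures with a two-sided .05.** The pooled-variance formula per group is

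n = [z_α √(2 p̄(1 − p̄)) + z_β √(p1(1 − p1) + p2(1 − p2))]² / (p1 − p2)².

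- Written against audio: p̄ = .175, so the roots are √.28875 = .5374 and √.2775 = .5268. The bracket is 1.960 × .5374 + 0.842 × .5268 = 1.4965. Then 1.4965² / .0225 = 99.54, and 99.54 × 1.15 = 114.5, which truncates to the stated 114.
- Written against control: p̄ = .06, so the roots are √.1128 = .3359 and √.1096 = .3311. The bracket is 1.960 × .3359 + 0.842 × .3311 = .9369. Then .9369² / .0064 = 137.15, and 137.15 × 1.15 = 157.7, which truncates to the stated 157.

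The unpooled two-sided formula, divided by 0.85 for loss, gives 115 and 159, also close.

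**2. Try a one-sided .05.**

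| One-sided formula | Written/audio (stated 114) | Written/control (stated 157) |
|---|---|---|
| Pooled, × 1.15 (from 78.29 and 107.92) | 90.0 | 124.1 |
| Pooled, rounded up, ÷ 0.85 | 93 | 128 |
| Unpooled, ÷ 0.85 | 91 | 125 |
| Pooled with continuity correction, ÷ 0.85 | 109 | 156 |

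The last row comes near 157 but misses 114. None of these gives both figures, so a two-sided .05 is the reading that fits.

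**3. What one tail does to the t test.** This step assumes that the test is run at .05, because the analysis section gives no level.

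- The critical value (large-sample) falls from 1.960 to 1.645.
- The chance of a false claim in the favoured direction rises from .025 to .05, the same bar as a two-sided .10 test.
- The chance of a false claim in the other direction falls from .025 to 0.
- Total type I error is therefore .025 + .025 = .05 two-sided and .05 + 0 = .05 one-tailed. It does not change.
- If the level were .025 one-tailed, the favoured-direction rate would also stay at .025.

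**4. Power.** A comparison with 80% power at a two-sided .05 has power Φ(1.960 + 0.842 − 1.645) = Φ(1.157) = 87.6% when tested one-tailed at .05 in the favoured direction.

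**The case against.** The best defence is that the protocol does expect a direction. It considers audio more suitable for people who cannot read, and the sizing expects more improvement with audio than with written material, and more with written material than with no intervention. That explains why a one-tailed test might have been chosen, but an expectation does not rule out interest in the opposite result, and the objective leaves the question open.

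It can also be said that the sentence follows the demographic profile and speaks of differences between participants, so it may concern baseline characteristics only. Its use for outcomes is likely, since the next sentence deals with total scale scores, but it is not explicit. This limits the reach of the point without removing it: for baseline comparisons between randomised arms there is no expected direction of imbalance, and one tail has no basis there either.

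Four stronger readings are tempting, and the document does not support them:

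- A reader might infer that the type I error doubles to 10%. It does not. Only the favoured-direction share doubles, and only if .05 is the level used.
- A reader might infer that the protocol declares its sample size two-sided and then contradicts it. Sidedness is never stated; it is inferred from the arithmetic.
- A reader might infer that the sample size is wrong for the planned test. The sized comparison is of proportions, which the chi-square and z tests would handle. The t test does not govern it and is itself one of two options for continuous variables.
- A reader might infer that the trial could not reveal a worse result. No direction is stated, so it is unknown which result would be missed. The planned effect sizes, confidence intervals and group summaries would still show it. What is lost is a significant t-test result in that direction.

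**Conclusion.** The point stands in a limited form. The protocol fixes a one-tailed t test as an option for continuous differences between arms, without direction, level or reason. That choice does not match the open question in the objective, the other named tests, or a sample size that the arithmetic shows to be two-sided. Because it is a stated rule, it is more than detail left to an analysis plan.

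Its size is a favoured-direction false-positive rate of .05 instead of .025, with total type I error unchanged at .05, and no significant t-test result possible in the other direction. This rests on three assumptions: .05 is the level applied to the t test, the sentence covers outcome scores, and the t test rather than Mann-Whitney is chosen. The rates are nominal and take the test's independence assumption as given; how clustering by LGA is handled is a separate matter. The comparison of proportions that set the sample size is not affected.

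**What to change.** In the data analysis section, replace the one-tailed label with a statement that all comparisons between arms (t, Mann-Whitney, chi-square and z) are two-sided at .05, and report two-sided 95% confidence intervals for the differences. State in the sample size section that .05 is two-sided, if the sponsor confirms that this was intended.

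The sample size stays at 114, 114 and 157 per region, because those figures already fit two-sided testing. The price is nominal power for continuous scores in the favoured direction: a comparison with 87.6% power one-tailed has 80% two-sided. The Results section says that data analysis had not begun at submission, so on the document's own account the change could be made before any results were seen.

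### Backward stepwise elimination chooses the factors said to have an independent effect, so the final model's p-values and intervals ignore that selection and weak confounders can be dropped

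*Protocol article*

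**What the plan says.** The Data Management and Data Analysis section of the protocol article fixes the method and the reading of its result: "Stepwise multivariate regression with backward elimination will be done to examine what factors will have an independent effect on the outcomes". The result is not labelled exploratory. On software it says "Data analysis will be done in the software package SPSS Statistics (SPSS Inc"), and it names no method that allows for selection.

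The same section plans the arm comparisons separately: unadjusted two-group tests, a z test on change, and a comparison of audio with written at follow-up. Quantile regression is held in reserve for demographic differences between arms. The article does not say whether study arm is a term in the stepwise model.

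Two design facts bear on the point. Under Participant Recruitment and Follow-Up, "each LGA will have either the audio-delivered or the written intervention or be a control group", so each state contributes one local government area (LGA) per arm. The Introduction lists age, gender, occupation, education and living area as characteristics already linked to community stigma about leprosy.

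**The concern.** A factor has an independent effect if its coefficient is non-zero given the other factors. Backward elimination answers this from a model that the same data selected by discarding non-significant terms. The ordinary p-values and intervals of that final model take no account of the search.

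Two harms can follow. First, a term may be called independent merely because it survived, above all if the removal threshold is looser than 0.05. Second, elimination judges each covariate by its own p-value, not by how much it confounds. With one LGA per arm per state, participant characteristics may differ between arms. Several covariates can each be too weak to stay and yet matter jointly. If arm is in the model, its coefficient then absorbs what was dropped.

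This is also the only multivariable model planned unconditionally, since the quantile regression applies only if judged necessary.

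**Working it through.** **Inputs from the article.** "114 in the audio intervention group, 114 in the written material intervention group, and 157 in the control group in each region", with 15% loss to follow-up and a significance level of .05.

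The plan's group sizes reproduce from the usual two-proportion formula (two-sided 0.05, power 80%):
- 10% against 25%: 99.5, and 99.5 × 1.15 = 114.5 (stated 114).
- 10% against 2%: 137.2, and 137.2 × 1.15 = 157.7 (stated 157).

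Numbers left to analyse: 770 × 0.85 ≈ 655 in all; 2 × 114 × 0.85 ≈ 194 per intervention arm over both states. The article gives no error rate for the stepwise model, so there is no stated figure to reproduce for it.

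**Assumptions.** The number of candidates (8, 10 or 12), the removal threshold (0.05 or 0.10), the covariate slopes and the imbalances are not in the article. Ranges are shown.

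**Step 1. Factors with no effect.** With k independent null candidates, the chance that at least one has p below a is 1 − (1 − a)^k. Simulation used n = 655 and 2,000 runs per row.

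| k | 1 − 0.95^k | Full model, any p<0.05 | Elimination at 0.05, any kept | 1 − 0.90^k | Elimination at 0.10, any kept | Elimination at 0.10, any p<0.05 |
|---|---|---|---|---|---|---|
| 8 | 34% | 33% | 33% | 57% | 56% | 33% |
| 10 | 40% | 39% | 39% | 65% | 65% | 39% |
| 12 | 46% | 47% | 47% | 72% | 71% | 47% |

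Across repeated runs the 0.05 rates lie at about 32–46% and the any-kept rates at 0.10 at about 55–73%. The excess over a full model appears only when a term kept at p<0.10 is itself read as an effect.

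**Step 2. The arm effect, if arm is in the model.** Setting: 194 per arm, no true audio–written difference, no cluster variance, six covariates with slopes of 0.08–0.10 SD (0.09 in the mixed rows), 3,000 runs per setting. Omitting one covariate with slope 0.09 that differs by 0.5 SD shifts the arm coefficient by about 0.09 × 0.5 = 0.045 SD. The standard error of the arm difference is about √(2/194) = 0.10 SD. One omission is therefore minor, but several in the same direction are not.

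| Imbalance between arms | Full model | Elimination, arm may be dropped | Elimination, arm forced in |
|---|---|---|---|
| None | 5–6% | 5–6% | 5–6% |
| 0.3 SD, same direction | 5–6% | 8–9% | 8–13% |
| 0.3 SD, direction random by state | 5% | 6% | 6–7% |
| 0.5 SD, direction random by state | 5–6% | 8% | 8–9% |
| 0.5 SD, same direction | 4–5% | 10–13% | 12–16% (removal 0.10); 19–20% (removal 0.05) |

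A single covariate imbalanced by 0.5 SD gives only 5.5–5.9%. The inflation needs several weak prognostic factors that push the same way.

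**The case against.** Several stronger readings are tempting, and the documents do not support them.

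- **Stepwise selection manufactures chance findings.** At a 0.05 cut-off Step 1 shows no excess over a full model. That part is multiplicity, and keeping all terms does not remove it. This stands.
- **Intervals of retained factors cover the truth only about half the time.** Simulated coverage for null factors kept at p<0.10 is about 45–50%. This follows largely from conditioning on retention: about half of such factors also have p<0.05, so their intervals exclude zero. Significant null terms in a full model would show zero coverage by the same conditioning. The figure does not isolate a stepwise fault.
- **The trial's arm comparison has double the stated error rate.** The article never puts arm in this model, and its arm contrasts are separate tests. The LGAs are to be similar in literacy and endemicity, and allocation is random. Doubling needs the least favourable rows of Step 2.
- **No term is protected.** The article is silent on candidates, threshold and forced terms. An article may leave these to the full protocol or analysis plan, so the silence is no fault in itself.
- **A full model gives correct arm intervals.** It does not on this evidence. With two LGAs per arm, the 0.5 SD imbalance and assumed intracluster correlations of 0.01, 0.03 and 0.05, an individual-level full model has an arm error of about 12%, 26% and 37%, against 20%, 33% and 41% after elimination. Clustering dominates.

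What the objection leaves untouched is the sentence itself. It commits to selection by elimination and gives the result an inferential reading, and an analysis plan that followed it would inherit the problem.

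**Conclusion.** The point holds in a limited form and is worth changing, though it does not undermine the trial by itself. The final model's inference ignores the search that produced it, and elimination can discard confounders that are individually weak.

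- **Naming of factors:** about 55–73% of trials with 8–12 null candidates would name at least one if retention at an assumed p<0.10 is the criterion. At 0.05 there is no excess over a full model.
- **Arm effect, only if arm is in the model and clustering is ignored:** about 5% with balanced factors; roughly 6–10% with moderate or mixed-direction imbalance when arm may itself be dropped; about 11–12% with six same-direction 0.5 SD imbalances. Forcing arm in takes this last case to about 15% at a removal threshold of 0.10 and about 20% at 0.05.

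The candidate count, threshold, slopes, imbalances and the presence of arm in the model are all assumptions.

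**What to change.** Delete the words that call for stepwise selection and backward elimination, and substitute:

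> One prespecified model per outcome will contain arm, state, baseline value, age, gender, education or literacy, occupation, and rural or urban area. All terms are kept whatever their p-value. Estimates with 95% CIs come from this full model, and covariate associations are descriptive.

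Calling the covariate associations descriptive deals with the multiplicity that a full model still carries. The covariates are ones the trial collects or can derive, and the baseline value is available because the same participants are measured twice. About 655 analysed participants can support this many individual-level terms.

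The cost is a change of wording, slightly wider intervals and a longer coefficient table. The Results section says that data analysis had not begun at submission. Clustering by LGA must be handled separately, and the arm intervals from this model should not be called correct on the strength of this change alone.
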